## Abstract

This randomized controlled trial investigates the optimal dosing for post-stroke rehabilitation using repetitive transcranial magnetic stimulation (rTMS) and transcranial direct current stimulation (tDCS). Previous studies demonstrated improvements in cognitive and motor functions with specific intensities of rTMS and tDCS, but this trial explores various frequencies and currents to optimize therapeutic outcomes. A total of 128 post-stroke patients (within 1–6 months of stroke) with paraplegia or hemiplegia are recruited. Patients are divided into four groups for both rTMS (n = 49) and tDCS (n = 49): three groups with different stimulation intensities (1 Hz, 5 Hz, 10 Hz for rTMS; 0.5 mA, 1 mA, 2 mA for tDCS) and a sham control group. Along with this, there is a standard therapy group (n = 30) as control. Participants receive 20 min sessions, five days a week, over six weeks. Cognitive and motor assessments are conducted at 4 weeks, 6 weeks, and 6 months to measure short-term and sustained effects.•Hemodynamically stable post-stroke patients randomized in four groups in rTMS and tDCS each and their baseline cognitive and motor function assessed•Application of the two types of therapy for 6 weeks•Checking improvement of cognitive and motor function and compare the improvement among subgroups of recipient of various frequencies and currents

Hemodynamically stable post-stroke patients randomized in four groups in rTMS and tDCS each and their baseline cognitive and motor function assessed

Application of the two types of therapy for 6 weeks

Checking improvement of cognitive and motor function and compare the improvement among subgroups of recipient of various frequencies and currents

Specifications table

**Table utbl0001:** 

Subject area:	Neuroscience
More specific subject area:	Rehabilitation
Name of your protocol:	Neuromodulation
Reagents/tools:	(1) Montreal Cognitive Assessment (2) Fugl Meyer Assessment (3) Transcranial magnetic stimulation machine, Neuro-MS/D, Neurosoft LLC, Russia (4) High-definition transcranial direct current stimulation machine, Neurostim, Neurosoft LLC, Russia
Experimental design:	Double blinded randomized controlled trial
Trial registration:	CTRI/2024/05/*066729* registered at https://ctri.nic.in
Ethics:	Approved by Institutional Ethics Committee (2023–130-EMP-03). Patients will be recruited after taking written consent for voluntary participation.
Value of the Protocol:	Optimizes brain stimulation parameters (frequencies for rTMS and currents for tDCS) to enhance cognitive and motor recovery in stroke patients

## Background

Stroke is a major health concern worldwide, with its devastating effects leading to significant physical and cognitive disabilities in about 50 % survivors [1]. The journey toward recovery is long and challenging, requiring comprehensive rehabilitation strategies that aim to restore as much function as possible [2]. While various rehabilitation methods exist [3,4], there remains a search for more effective techniques that address both motor and cognitive deficits.

In recent years, non-invasive brain stimulation (NIBS) techniques, such as repetitive transcranial magnetic stimulation (rTMS) and transcranial direct current stimulation (tDCS), have gained attention for their potential to enhance stroke recovery [5,6]. These techniques use magnetic fields or weak electrical currents to modulate brain activity, promoting neuroplasticity—the brain's ability to reorganize itself after injury [7,8]. Neuroplasticity is crucial for recovery, as it allows the brain to form new neural connections and compensate for the damaged areas [9]. By stimulating or inhibiting specific regions of the brain associated with motor control or cognition, NIBS can enhance motor and cognitive functions [10].

Several studies highlight the potential of non-invasive brain stimulation techniques for stroke rehabilitation. Liu et al. demonstrated that 10 Hz TMS could improve daily living and attention functions, though long-term effects remain unexplored [11]. Yin et al. applied high-frequency rTMS to the left dorsal lateral prefrontal cortex, observing cognitive improvements without follow-up to assess lasting benefits [12]. A separate trial combining 5 Hz rTMS and cognitive training reported potential gains in cognition despite high dropout rates [13]. In contrast, low-frequency rTMS appeared more effective for motor and neurological recovery in ischemic stroke patients compared to high-frequency stimulation [14].

Studies on tDCS have also reported positive effects. Yan et al. found that tDCS benefits were more pronounced in patients with shorter disease durations, stressing the need for standardized protocols [15]. Research on bihemispheric tDCS combined with physical therapy indicated improvements in upper limb function, yet issues like lesion heterogeneity suggest that larger, long-term studies are required [16]. Despite promising outcomes, larger, blinded RCTs with better recruitment strategies are necessary to compare rTMS and tDCS efficacy and establish generalizability [17].

Despite the promise shown by NIBS in stroke rehabilitation [18], there is need of consensus on optimal frequencies and current for patients [19]. Research has demonstrated that factors such as frequency, intensity, and duration of stimulation play critical roles in determining the efficacy of these techniques [20]. However, the optimal combination of these parameters remains unclear, leading to inconsistent results across studies.

With this background, this study protocol was prepared for a clinical trial to address these critical gaps by exploring the optimization of rTMS and tDCS parameters in stroke rehabilitation.

## Description of protocol

### Patient allocation

Before the intervention, all participants undergo a comprehensive assessment to evaluate their baseline cognitive and motor functions. The cognitive assessment will be conducted using the Montreal Cognitive Assessment (MoCA) test, designed to measure a range of cognitive abilities such as memory, attention, and language skills. Motor function will be assessed using the Fugl-Meyer Assessment (FMA), which evaluates sensorimotor function in stroke patients. These baseline measurements are essential to determine each participant's starting level of impairment and to facilitate comparison with post-therapy outcomes.

Participants will be randomly assigned to one of three groups: (A) rTMS with standard therapy, (B) tDCS with standard therapy, or (C) standard therapy as the control group. The random allocation is shown Fig. 1. The patients in the active therapy group will receive the therapy with the pre-fixed protocol and patients in sham group will be provided with all settings of therapy with same time, but in a sham coil orientation for rTMS and 0.5 mA for initial and end 60 s with zero current in between for tDCS. The control group will receive only physiotherapy as the standard stroke rehabilitation therapy.

**Fig. 1 fig0001:**
[figure not shown]
Patient randomization and allocation.

To achieve this, researchers employ a randomized selection process using identically folded chits marked with group codes (e.g., a chit A-iii will allocate the patient to active rTMS of 10 Hz). Each participant selects a chit from a bowl, ensuring an unbiased distribution across groups and avoiding selection bias.

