## Limitations

This protocol has some limitations beyond our capability to adjust. Patient responses to non-invasive brain stimulation (NIBS) techniques like rTMS and tDCS can vary widely due to differences in brain structure, stroke severity, and neural plasticity. This variability can make it difficult to generalize optimal parameters across a diverse population. Additionally, the strict inclusion and exclusion criteria used to select participants may limit generalizability, as individuals with more severe impairments or certain comorbidities might respond differently to the treatment. Furthermore, the study uses fixed dosing parameters (frequencies and intensities) for rTMS and tDCS, which might not be optimal for each patient. Although necessary for research consistency, the lack of individualized dosing could limit the intervention's overall efficacy. Additionally, while the six-week intervention duration and single six-month follow-up provide insights into short- and medium-term effects, a longer follow-up period would be needed to determine lasting benefits. However, we are limited by the logistics of the study.

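### Stratifying the chit draw by time since stroke would cheaply reduce a common chance imbalance between dose arms of about 12 patients

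*Protocol article*

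**What the plan says.** The Abstract sets the entry window and total: "A total of 128 post-stroke patients (within 1–6 months of stroke) with paraplegia or hemiplegia are recruited". It gives 49 patients to rTMS and 49 to tDCS, each split over three doses and a sham, and adds that "there is a standard therapy group (n = 30) as control".

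The allocation text under Fig. 1 says that "researchers employ a randomized selection process using identically folded chits marked with group codes". Its example is a chit coded A-iii, which sends the patient straight to rTMS at 10 Hz. It continues: "Each participant selects a chit from a bowl, ensuring an unbiased distribution across groups and avoiding selection bias". The text names no stratum, block or minimisation factor. Fig. 1 itself is not available to this review.

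The Background reports from an earlier study that "tDCS benefits were more pronounced in patients with shorter disease durations". The Limitations section says that responses to stimulation "can vary widely due to differences in brain structure, stroke severity, and neural plasticity". Under Dosage comparison, the trial's conclusion is a recommended dose, and the lower setting is preferred if it proves equally effective.

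**The concern.** The trial ends in a choice among doses, made by comparing arms of about a dozen patients. The protocol itself cites time since stroke as related to the benefit of one of its two treatments, and each patient's value is known on entry because it is an eligibility condition. The allocation as described makes no use of it.

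With arms this small, a simple draw can leave one dose with clearly more early patients than another. If early patients improve more, through spontaneous recovery or stronger response, some of that advantage is credited to the dose. The same imbalance can also hide a real difference, which matters under a rule that favours the lower dose when results look equal.

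**Working it through.** **Inputs from the protocol.** Group sizes 49, 49 and 30; four arms per modality; entry at 1 to 6 months.
- Total: 49 + 49 + 30 = 128, which reproduces the stated figure.
- Patients per arm: 49 / 4 = 12.25, so about 12.

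**Assumed inputs.** The protocol gives neither the distribution of time since stroke nor the size of its effect. I take either 30 to 50% of patients as early, or entry times uniform over the window.

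**1. Counts of early patients.** Draw three dose arms of 12 as Binomial(12, p) and record the largest difference between any two (400,000 simulated trials per row).

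| Early fraction p | Largest gap ≥ 3 of 12 | Largest gap ≥ 4 of 12 | Two given arms, gap ≥ 4 of 12 |
|---|---|---|---|
| 0.3 | 50% | 26% | 12% |
| 0.4 | 55% | 31% | 14% |
| 0.5 | 56% | 32% | 15% |

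Drawing without replacement from 128 gives nearly the same (26% at p = 0.3 and about 33% at p = 0.5 for a gap of at least 4). It therefore matters little that the protocol does not say whether chits are replaced.

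**2. Mean time since stroke.** For a uniform distribution on 1 to 6 months:
- SD = (6 − 1)/√12 = 1.44 months.
- SE of the difference between two arms = 1.44 × √(2/12) = 0.59 month, so the 95% chance range is ±1.96 × 0.59 = ±1.15 months.
- Simulated largest gap among three arms: over 0.5 month in 67.5% of trials and over 1 month in 20.5%.

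**3. Effect on the ranking of doses (assumed correlations).** Let time since stroke correlate 0.3, 0.5 or 0.7 with the outcome. Compare the dose that ranks first with the dose that would rank first if the time component were removed entirely.
- Three equally effective doses: the top rank changes in 14%, 24% or 35% of trials.
- One dose better by 0.5 SD: it changes in 7%, 12% or 16%. The better dose ranks first in about 82% of trials without balance, and in 83%, 86% or 92% with the time component removed.

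**4. What stratifying achieves.** Take two strata, each with blocks of 21 chits: 8 × 2 = 16 for the dose and sham arms, plus 5 for standard therapy. The chit ratio is 5/2 = 2.5, against a planned 30/12.25 = 2.45. Six full blocks give 12 per arm and 30 controls, which is 126 patients. With 128 patients and 30 to 50% early (20,000 runs per setting):
- Early counts among three dose arms differed by 2 or more in 11 to 18% of trials and never by 3 or more.
- Dose-arm sizes differed by 3 or more in about 7 to 11% of trials and never by 5 or more.
- For comparison, one large bowl of 64 chits per stratum, refilled when empty, left dose-arm sizes differing by 3 or more in about 12 to 54%. The small blocks are therefore needed.

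**The case against.** The strongest reply is that randomisation is sound as it stands. The allocation text claims an unbiased distribution, not a balanced one. A fair draw is unbiased in expectation, type I error is not inflated, and ordinary standard errors already cover chance imbalance. All of that stands. A reader might infer that the sentence under Fig. 1 is false or that the dose comparison is biased; the documents support neither.

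A reader might also take the opening of the Limitations section, "This protocol has some limitations beyond our capability to adjust", as saying that such variation cannot be adjusted for in the analysis. It introduces a general list that also covers eligibility, fixed dosing and length of follow-up. The item on varying response concerns generalisability and does not name time since stroke. It need not be deleted.

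Three further limits stand. The cited modifier concerns tDCS only, with no effect size or time range; for rTMS the argument rests on spontaneous recovery, which the protocol does not discuss. Covariate adjustment would deal with much of the problem and may sit in an analysis plan that is not shown. The 26 to 32% figure is for the worst pair of three arms; for two given arms it is 12 to 15%.

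The objection does not remove the point. The article does describe how patients are allocated, and that method leaves unused a variable which is known at entry and which its own Background singles out.

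**Conclusion.** The point holds as a cheap improvement, not as an error. Under the described draw, a gap of at least 4 of 12 early patients among the three dose arms of a modality occurs in about 26 to 32% of trials, assuming 30 to 50% enter early. That adds noise to the dose comparison. Under assumed correlations of 0.3 to 0.7, it changes the top-ranked dose in 7 to 16% of trials when one dose is truly better by 0.5 SD. The larger figures of 14 to 35% apply when all doses are equal and no ranking is correct. The imbalance figures need only the arm size and the early fraction. The ranking figures rest on correlations that nothing in the documents anchors, and they measure complete removal of the time component, which two strata would only approach. Stratifying does not cure the underlying weakness of about 12 patients per arm.

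**What to change.** In the allocation text under Fig. 1, for patients not yet allocated, stratify the draw by time since stroke. Use two strata with a cut stated in advance within the 1 to 6 month window; about 3 months would serve as an example. In each stratum use small blocks of chits in the planned arm ratio, for example 2 for each dose or sham arm and 5 for standard therapy. Refill only when a block is used up, and do not let staff see the remaining chits.

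Include time since stroke, as the stratification factor, together with the baseline score in the between-dose comparison, if the analysis plan does not already do so. This step also helps for patients already allocated.

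The cost is a sentence or two of text and slightly more handling of chits, with no extra patients, visits or assessments. There are two downsides. Dose-arm sizes may differ by a few patients if a stratum ends mid-block, and allocation becomes somewhat predictable near the end of a block. With arms this small, do not add more than one further stratification factor.

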### Therapy

#### Active rTMS group

This group receives repetitive transcranial magnetic stimulation (rTMS), where magnetic pulses target the motor cortex. The intervention follows three frequency settings (1 Hz, 5 Hz, and 10 Hz) to identify the optimal dose for effectiveness. The 1 Hz therapy will be provided on the contralateral side of the affected side while other will be provided on the affected side (Fig. 2).

**Fig. 2 fig0002:**
[figure not shown]
Therapy intensity for repeated transcranial magnetic stimulation.

Low-frequency magnetic stimulation, typically <5 Hz, is known to reduce cortical excitability, producing an inhibitory effect on brain activity. The 5 Hz and 10 Hz therapy will be provided on the affected side of the cortex. Higher frequencies of magnetic stimulation, such as 5 Hz and 10 Hz, are considered to have excitatory effects on brain activity, increasing cortical excitability. In sham therapy, the coil will be placed on the side of the affected cortex.

At the beginning of the study, the resting motor threshold (RMT) of each participant will be established using the software's calibration tools. The RMT is the lowest stimulation intensity at which thumb movements are observed in at least 5 out of 10 pulses delivered to the contralateral motor hotspot. Then, the stimulation frequency, intensity (80 % of the MT), and train duration will be selected as per the prefixed protocol. The first therapy protocol is shown in Fig. 3, and the rest of the protocol is shown in Table 1.

**Fig. 3 fig0003:**
[figure not shown]
First rTMS protocol showing the intensity, pulses, and trains.

**Table 1 tbl0001:** Details of the protocols for the intervention group (Group A) of rTMS.

Frequency (Hz)	Intensity (% of RMT)	Session duration (min)	Train duration (seconds/train)	Inter-train interval (if any, sec)	Number of trains per session	Number of sessions	Number of pulses/sessions	Stimulation site
1	80	20	1200	Continuous	1	30	1200	Ipsilateral
5	80	20	10	20	40	30	2000	Contralateral
10	80	20	5	25	40	30	2000	Contralateral

RMT: Resting motor threshold.

#### Sham rTMS group

For sham stimulation, the figure-of-eight coil can be tilted 45° from the scalp, with both wings touching the head (Fig. 4) [21]. This orientation minimizes cortical stimulation, prevents the induction of motor-evoked potentials (MEPs), and effectively replicates the sensory and auditory effects of active TMS.

**Fig. 4 fig0004:**
[figure not shown]
rTMS coil position in sham treatment.

#### Active tDCS group

Participants receive conventional transcranial direct current stimulation (tDCS) on the motor cortex. For the therapy, the anode is placed on the primary motor cortex on the lesioned side, and the cathode is placed on the contra-lateral supraorbital area. The dosage settings vary in current intensity (0.5 mA, 1 mA, and 2 mA), as shown in Fig. 5.

**Fig. 5 fig0005:**
[figure not shown]
Therapy intensity for transcranial direct current stimulation.

The software interface for the first therapy is shown in Fig. 6. In this protocol, the therapy will be provided with an amplitude of 0.5 mA for 20 min. The current will be provided with a ramp up and ramp down of two minutes in initial and ending of the time, respectively.

**Fig. 6 fig0006:**
[figure not shown]
The amplitude, duration, and ramp time of first therapy protocol of active tDCS.

The patient's scalp is prepared for electrode placement by slightly rubbing the scalp with electrode gel, and the electrodes are encased in 0.9 % saline-soaked sleeves. These sleeve-enclosed electrodes are placed on the scalp as close as possible and fastened by rubber fasteners. If the patient is having a lesion on the left hemisphere and the anode is placed on the left primary motor cortex area. The cathode is placed on the supraorbital area on the right side. The therapist can set the protocol on the controlling computer when the tDCS device is connected to the computer by a USB. The device can also be operated from the user interface of the device itself (having control keys and display) when the computer is not available.

#### Sham tDCS group

The sham tDCS group will be provided with the electrode placed exactly on the motor cortex and supraorbital region with the application of a saline-soaked sleeve of electrode just like the active group. A current of 0.5 mA will be applied for the initial and the final 60 s and zero current will be delivered for the rest of the session. This approach ensures that participants perceive the initial sensations associated with tDCS, such as tingling or itching, thereby maintaining blinding in controlled studies.

For all the active and sham groups, the session will last for 20 min, five days a week, across six weeks. This structured schedule allows for consistent and comparable intervention times across all groups.

#### Standard therapy group

This group will receive only physiotherapy as the standard stroke rehabilitation therapy. This group will be serving as the control group of the study. Physiotherapy includes a combination of functional, aerobic, and resistance exercises 20 min. In addition to this, the drug therapy as prescribed by the treating physician will be continued by the patients.

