#### Dosage comparison

In both the rTMS and tDCS groups, the intervention is applied at three different dosage levels to identify the most effective parameters for enhancing cognitive and motor outcomes. The response to each dosage is compared across groups, considering factors such as accuracy of motor function improvement, cognitive gains, and patient tolerance. This comparative approach aims to optimize the therapeutic dose, balancing efficacy with safety. If a lower frequency or amplitude is found to be equally effective to a higher frequency or amplitude, then the study will conclude by recommending a lower frequency or amplitude.

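### Two controls are named but not ranked, and the lower-setting rule does not state that a setting must first beat sham

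*Protocol article*

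**What the plan says.** The Abstract describes three active settings per modality "and a sham control group. Along with this, there is a standard therapy group (n = 30) as control". Both kinds of arm are therefore called controls.

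The body is less even. Patient allocation lists three main groups, the last being "C) standard therapy as the control group", and treats sham as part of the rTMS and tDCS groups. Under Standard therapy group the article says "This group will receive only physiotherapy as the standard stroke rehabilitation therapy" and then "This group will be serving as the control group of the study". The sham sections describe coil tilt, electrode placement, current and the blinding purpose. They do not say what sham will be compared with.

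The specifications table calls the study a "Double blinded randomized controlled trial".

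Dosage comparison says that the response to each dosage is compared across groups, considering motor gain, cognitive gain and tolerance. It then fixes one rule: where a lower frequency or amplitude proves as effective as a higher one, "then the study will conclude by recommending a lower frequency or amplitude". No margin is given for equal effectiveness, and neither sham nor standard therapy appears in the rule.

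**The concern.** Two things are at stake.

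The first is what an efficacy estimate would mean. The stimulation arms receive standard therapy plus device sessions of 20 minutes, five days a week for six weeks. The standard therapy arm receives no device, and its participants cannot be blind to that. A difference between an active arm and standard therapy therefore contains any stimulation effect together with expectation and about 30 × 20 = 600 minutes of added contact. A difference between an active arm and its own sham largely removes the last two. A reader who takes the title of control group at face value will use the wrong contrast to judge efficacy.

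The second is the recommendation. The rule compares active settings with each other. If every setting in a modality does no more than sham, its condition is met, and the trial concludes with a recommended setting that has not been shown to work.

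**Working it through.** **Inputs from the article.** Total 128; 49 in rTMS, 49 in tDCS, 30 in standard therapy; four arms per modality (Abstract).

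**Stated figure.** 49 + 49 + 30 = 128, which reproduces. Arm size is 49 / 4 = 12.25, so 12 or 13. I use 12.

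**Assumptions, because the article gives no figure.** Two-sided alpha 0.05, normal outcome with SD 1, two-sample t-tests, no dropout, and equal effectiveness read as a non-significant difference.

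**Step 1: logic.** Let the three settings and sham have the same true mean. Each setting is then exactly as effective as the others, the condition of the rule is true, and the lowest setting is recommended. This step needs none of the assumptions.

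**Step 2: how often it happens in data.** Simulation under no effect, three active arms of 12:

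| Reading of the rule | Lowest setting recommended |
|---|---|
| Neither higher setting is significantly better than the lowest | about 95% |
| Lowest does not differ significantly, in either direction, from both higher settings | about 91% |
| All three pairs are non-significant | about 88% |

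If the lowest setting must also be significantly better than sham, the frequency falls to about 2% (1.6% with all pairs non-significant, 2.3% on the sham test alone).

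**Step 3: does standard therapy protect instead?** Suppose active and sham share a non-specific gain over standard therapy, and stimulation itself adds nothing. The size of the gain is assumed.

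| Shared gain (SD) | Pooled active (36) significantly better than standard therapy (30) | At least one setting (12) significantly better than standard therapy |
|---|---|---|
| 0.2 | 12% | 20% |
| 0.3 | 22% | 31% |
| 0.5 | 51% | 58% |
| 0.8 | 89% | 89% |

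Pooled active versus sham stays at about 2.5% in the favourable direction throughout.

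**Step 4: cost of requiring superiority to sham.** 95% CI half-widths in SD units:

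- 12 versus 12, unadjusted: t(22) × √(2/12) = 2.074 × 0.408 = 0.85.
- 12 versus 12, Dunnett for three contrasts with SD pooled over four arms (simulated critical value about 2.43): 2.43 × 0.408 = 0.99.
- 12 versus 30, standard therapy: t(40) × √(1/12 + 1/30) = 2.021 × 0.342 = 0.69.

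Power for one setting against sham:

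| True effect (SD) | Unadjusted | Dunnett |
|---|---|---|
| 0.5 | 22% to 23% | 12% to 13% |
| 0.8 | 47% to 50% | about 33% |

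In the unadjusted column the lower value uses the t distribution and the higher the normal approximation. The range in the Dunnett column is simulation error.

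**The case against.** The case against the concern is substantial. Sham is called a control in the Abstract, its sessions are matched to the active ones in length and schedule, and a comparison across groups may well include it. This is a condensed article. The primary contrast, the multiplicity method and the order of testing usually sit in the full protocol or SAP, which are not shown. The lower-setting sentence can also be read as a tie-breaker between settings already known to work, since Dosage comparison speaks of finding the most effective parameters and of balancing efficacy with safety.

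Much of this stands, and it rules out stronger readings that a reader might infer:

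- That the trial lacks a sham reference, or will judge efficacy only against standard therapy. The article says neither. It labels two controls and does not rank them.
- That the trial rejects any efficacy condition. The condition is unstated in the rule, and it may have been meant.
- That 95% is the error rate of the rule as written. The article never equates non-significance with equality and states no alpha. The figure moves between 88% and 95% with the reading.
- That the standard therapy arm is wholly unblinded. Only participant unblinding follows from physiotherapy-only care. Outcome assessors could still be blind.

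What the objection does not remove is the rule. It is stated in this document, with its condition and its consequence. A sham test in an unseen SAP would not change a recommendation that does not depend on that test.

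**Conclusion.** The point holds in a limited form. The article leaves open which of its two controls is the efficacy reference, and its recommendation rule can be satisfied by settings that all equal sham. The second part follows from the wording alone. Its size, about 88% to 95% of null trials against about 2% with a sham condition, rests on the assumed alpha, 12 per arm, and non-significance taken as equality. The Step 3 figures rest on an assumed non-specific gain. The matter is worth correcting because the dose recommendation is the stated purpose of the trial, but it calls for clarification and does not show that the design lacks a valid control.

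**What to change.** In Patient allocation and Standard therapy group, state that the efficacy reference for each active setting is the sham arm of its own modality, and that standard therapy is a secondary comparison in which participants are not blinded. In Dosage comparison, add that the lower-setting rule applies only to settings shown superior to their sham, and that otherwise no setting is recommended. Say there what counts as equally effective, preferably as a margin. The multiplicity method can be left to the SAP.

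No arm, treatment or visit changes, but what the trial can conclude does. Against sham the interval is wider than against standard therapy, and the power figures above mean that moderately effective settings would often fail the condition, more often still with multiplicity adjustment. The sponsor should accept openly that no recommendation is a likely outcome at this sample size.
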